## Abstract

**Background:**

Spinal cord injury (SCI) is associated with autonomic imbalance and significant secondary conditions, including cardiac and brain dysfunction that adversely impact health and wellbeing. This study will investigate the effectiveness (intention-to-treat) of a neuro-cardiac self-regulation therapy to improve autonomic and neural/brain activity in adults with SCI living in the community.

**Methods:**

A two-arm parallel, randomised controlled trial in which adults with SCI living in the community post-rehabilitation will be randomly assigned to a treatment or control group. The treatment group (*N* = 60) aged 18–70 years with a chronic traumatic or non-traumatic SCI, will receive intervention sessions once per week for 10 weeks, designed to regulate autonomic activity using computer-based feedback of heart rate variability and controlled breathing (called HRV-F). Comprehensive neurophysiological and psychological assessment will occur at baseline, immediate post-treatment, and 6 and 12-months post-treatment. Primary outcome measures include electrocardiography/heart rate variability (to assess autonomic nervous system function) and transcranial doppler sonography (to assess cerebral blood circulation in basal cerebral arteries). Secondary outcomes measures include continuous blood pressure, electroencephalography, functional near-infrared spectroscopy, respiration/breath rate, electrooculography, cognitive capacity, psychological status, pain, fatigue, sleep and quality of life. Controls (*N* = 60) will receive usual community care, reading material and a brief telephone call once per week for 10 weeks and be similarly assessed over the same time period as the HRV-F group. Linear mixed model analysis with repeated measures will determine effectiveness of HRV-F and latent class mixture modelling used to determine trajectories for primary and selected secondary outcomes of interest.

**Discussion:**

Treatments for improving autonomic function after SCI are limited. It is therefore important to establish whether a neuro-cardiac self-regulation therapy can result in improved autonomic functioning post-SCI, as well as whether HRV-F is associated with better outcomes for secondary conditions such as cardiovascular health, cognitive capacity and mental health.

**Trial registration:**

The study has been prospectively registered with the Australian and New Zealand Clinical Trial Registry (ACTRN12621000870853.aspx).

Date of Registration: 6th July 2021.

Trial Sponsor: The University of Sydney, NSW 2006.

Protocol version: 22/07/2021.

## Background

Spinal cord injury (SCI) is associated with damage to the nervous system and spinal cord as a result of bruising, compression or severance following a traumatic injury [1], or with deterioration of the spine, infection, vascular accident, or tumours in non-traumatic disease [2]. People with SCI also have higher risks of secondary health conditions, including sleep disorder [3, 4], psychological distress [5, 6], chronic pain [6, 7], elevated fatigue [8], cognitive impairment [9, 10] cardiovascular morbidity [1, 11] and autonomic nervous system dysfunction [1, 4, 11]. Dysfunctional autonomic activity after SCI impacts various bodily functions, including cardiac and brain function. However, treatment options and research targeting autonomic dysfunction after SCI are still limited.

Recently, there has been focus on restoring autonomic function in people with SCI using transcutaneous or surgically implanted epidural stimulation technology of the thoracolumbar cord [12, 13]. Preliminary studies have shown favourable results, such as temporary improvements in cardiovascular and motor function [12, 13]. However, there has been scarcely any research investigating benefits of non-invasive neuro-cardiac self-regulation interventions that could enhance neuroplasticity and improve autonomic/neural function following a SCI. Neuro-cardiac self-regulation (HRV-F) usually involves participants learning to regulate their autonomic neuro-cardiac activity via computer/mobile app-based feedback of heart rate variability (HRV) combined with instruction on slow/diaphragmatic breathing, with sessions delivered once per week for between 6 and 10 weeks [14]. Research has shown such neuro-cardiac self-regulation therapy to be a promising treatment for anxiety, depressive mood and trauma-related distress [15], asthma [16], pain [17], and heart disease [18].

The presumed mechanism for benefits associated with self-regulation of the autonomic nervous system involves a combination of physiological processes resulting in strengthening of baroreflex homeostasis, vagal afferent pathways, and phase relationships between blood pressure, heart-rate and brain connectivity [19–22]. Optimal autonomic regulation is associated with healthy functioning of the body’s major systems, particularly cardiac and brain function (e.g., cognitive and psychological aspects) [11, 19–22]. Following a SCI, serious cardiovascular complications are a major concern, such as unstable blood pressure control related to episodes of orthostatic hypotension and autonomic dysreflexia (AD), characterized by critical blood pressure rises and associated bradycardia [23–25]. Benefits of improved autonomic self-regulation could therefore be substantial for people with SCI, including reduced cardiovascular morbidity associated with autonomic aetiology, orthostatic instability, severity of AD, and improved cognitive functioning, mental health, pain, vitality and sleep [4, 11–13]. Furthermore, this study may lead to improved understanding of the physiological underpinning of brain-autonomic dysfunction and the influence of top down/bottom up controls related to neuroplasticity [22].

Evidence that autonomic activity changes after a SCI and during autonomic challenges suggests autonomic modulation may be a new frontier for improving neuro-cardiac function in individuals with SCI and may mitigate maladaptive plasticity [11]. Underlying hypotheses are the development of intrinsic spinal rhythmicity within the injured cord or recovery of supraspinal pathways [22], demonstrating that autonomic activity measured by HRV in adults with SCI is imbalanced, very different to able-bodied individuals [26]. For example, groups with tetraplegia and paraplegia both have significantly reduced low frequency (LF) HRV activity and impaired sympatho-vagal control [26] and this autonomic imbalance was associated with sleep disorder and fatigue in SCI [4, 26, 27]. It has also been shown that after participating in a 40-min resting/cognitive task, adults with high lesions (at/above T3 level) significantly increased the standard deviation of the average normal-to-normal intervals (SDNN) in the HRV in the LF band (0.04–0.15 Hz) in comparison to an able-bodied cohort [4], suggesting that low frequency autonomic activity in this group is modifiable.

Dysfunctional brain/neural activity is also reported after SCI, in terms of altered brain activity and connectivity [28–32], cerebral blood circulation [33] and cognitive impairment [9, 10]. Research has shown that brain activity is related to HRV activity, clarifying mechanisms of heart-brain neurovisceral relationships [28, 29]. For example, in non-SCI samples, HRV biofeedback improved cognitive and brain activity [29] while increases in the 8–12 Hz electroencephalography (EEG) range (called alpha activity) resulted in changes in HRV [28]. Additionally, adults with SCI have increased risk of thalamocortical dysrhythmia, that is, brain activity characterized by low frequencies (theta/low alpha) similar to aged brain activity in frailty [30, 31]. Furthermore, it is important to improve regulation of cerebral blood flow to compensate for the life-threatening variations in the movement of blood through the circulatory system associated with SCI [33]. It is therefore feasible that HRV self-regulation therapy could result in improved cerebral blood flow, EEG activity, brain metabolism and cognitive capacity in adults with SCI.

The primary objective of this research is to establish the effectiveness of a self-regulation intervention (HRV-F) to improve autonomic/neuro-cardiac function in adults with SCI, that is, improved autonomic regulation and brain/neural activity, such as cerebrovascular circulation and brain connectivity. Secondary objectives involve determining whether HRV-F results in improvements in associated functions such as mental health, cognitive capacity, vitality/fatigue, pain and sleep. While there is limited evidence that HRV-F will achieve these objectives in adults with SCI [12, 21], the scientific basis for our objectives is compelling. This includes: (i) the fact that a healthy autonomic nervous system is of vital importance for daily functioning given it regulates the respiratory, cardiovascular, digestive, endocrine and neural systems [32]; (ii) we have demonstrated functional/adaptive changes in autonomic activity in adults with chronic SCI (i.e., increased HRV) [4]; and (iii) systematic review and meta-analytic evidence concluded HRV-F is an effective self-regulatory intervention for conditions such as depression, heart disease and other clinical conditions in non-SCI populations [15, 18, 34, 35]. This research will address evidence gaps about improving autonomic/neural function in people with SCI, especially in higher and complete lesions. It will also develop a strategic plan for translating findings to those individuals with SCI living in the community with disability and at-risk from secondary conditions like orthostatic instability and AD.

## Methods

### Study design

The design is a two-arm parallel, intention-to-treat, prospective single-blind randomized controlled trial (RCT).

### Objectives

#### Primary objectives

To establish the effectiveness of a self-regulation intervention (HRV-F) to improve autonomic/neuro-cardiac function in adults with SCI. Autonomic/neuro-cardiac function includes autonomic regulation and brain/neural activity, such as cerebral vascular perfusion and brain connectivity.

#### Secondary objectives

To determine whether HRV-F results in improvements in associated secondary conditions, such as mental health, cognitive functioning, fatigue, pain, and sleep.To conduct a translation implementation study composed of interviews and a readiness to change survey with a broad range of stakeholders.

### Participants

Participants in the RCT will include 120 adults with a chronic SCI living in the community. Inclusion criteria include: (i) aged 18–70 years with SCI living in New South Wales (NSW), Australia; (ii) English speaking; (iii) traumatic/non-traumatic aetiology with complete/incomplete lesions; (iv) at least 12-months post-injury. Exclusion criteria consist of: (i) evidence of severe cognitive impairment as determined by a neurocognitive screen; (ii) evidence of severe respiratory disorder or impaired respiratory function; (iii) evidence of severe psychiatric disorder, such as bipolar disorder or psychoses, determined by psychiatric assessment, and (iv) taking prescribed ß-blockers. Participants for the implementation study will include up to 100 stakeholders and health professional participants. Stakeholders include individuals from relevant government departments and SCI advocacy groups. Health professionals will include those involved in rehabilitation in the hospital and community settings. Participant recruitment for the implementation study will involve convenience sampling through the NSW Agency for Clinical Innovation State SCI Service (SSCIS) Network and personal contacts in relevant health settings.

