### Physiological assessment

See Table 1 for all primary and secondary outcome measures and endpoints (baseline versus 10 weeks, 6 and 12 months) for the RCT and implementation phase. The physiological assessment protocol includes:
(i)Activity #1: 5-min resting baseline (spontaneous breathing) after 2-min habituation;(ii)Activity #2: 5-min Stroop test;(iii)Activity #3: 5-min recovery (spontaneous breathing);(iv)Activity #4: 5-min breathing task (paced breathing at around 6 breath/minute);(v)Activity #5: 5-min recovery (spontaneous breathing).

**Table 1 Tab1:** Schedule of activities and measures for the RCT and implementation study. All psychometric instruments are scientifically validated and reliable

PROJECT STAGE *(number of participants)*			RCT (***N*** = 120) Pilot and main study phase)						Implementation phase (***N*** = 100)
**TIMELINE/PHASES***(D- day, W: week; M: month; Ph: phase)*			**-7D to 0D**	**0D**	**10 W**	**6 M**	**12 M**	**Fortnightly**	**Ph-1 to Ph-5**
**RECRUITMENT**	**ACTIVITIES**	**Mode of data collection**							
Screening	Eligibility checklist	In-person	**✓**						
	ISCoS cardiovascular function dataset	In-person	**✓**						
	ISCoS pulmonary function basic data set	In-person	**✓**						
Consent procedure	Informed consent procedure	In-person	**✓**						
**PARTICIPANT DESCRIPTORS**	**ASSESSMENTS**	**Mode of data collection**							
Socio-demographics	Socio-demographics details	In-person or online		**✓**					
Pre-injury details	Employment history and psychological status	In-person or online		**✓**					
Medical history	Self-report past/present health history	In-person or online		**✓**					
Injury characteristics	Level of lesion, AIS and FIM	Medical records		**✓**					
Pulmonary function	Pulmonary function test	In-person		**✓**					
**ALLOCATION**	**DESCRIPTION**	**Mode**							
Intervention group	HRV-F + Usual care	In-person and online							
Control group	Usual care	Online							
**PRIMARY OUTCOMES**	**OUTCOME MEASURE**	**Mode of data collection**							
Autonomic function	ECG/ HRV Time domain – Short term	In-person		**✓**	**✓**				
	ECG/ HRV Frequency domain – Short term	In-person		**✓**	**✓**				
Cerebral basal artery blood flow	Doppler assessment – Short term	In-person		**✓**	**✓**				
**SECONDARY OUTCOMES**	**OUTCOME MEASURE**	**Mode of data collection**							
Autonomic function	ECG/ HRV Time domain – Long term	In-person		**✓**		**✓**	**✓**		
	ECG/ HRV Frequency domain – Long term	In-person		**✓**		**✓**	**✓**		

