### Primary physiological outcome measures

Electrocardiography (ECG) assessment from which HRV will be calculated at 10 weeks (short-term effect), in order to determine whether HRV-F results in improved autonomic nervous system function. HRV via ECG (electrodes on chest, modified lead II configuration) will be measured using the PowerLab 8/35 8-channel, 16-bit resolution recorder data acquisition system with programmable gain and two galvanically-isolated channels FE232 Dual Bio Amps (ADInstruments, www.adinstruments.com). A sampling rate of 512 Hz will be used for time/spectral analyses [4]. HRV signal processing will be performed using Kubios HRV Premium software (Version 3.3.1, University of Kuopio, Finland). HRV indexes neuro-cardiac function/regulation, generated by bidirectional heart-brain interactions (i.e., top-down influences on cardiac and peripheral physiological processes and bottom-up influences on central control mechanisms) and dynamic non-linear autonomic nervous system (ANS) regulation. HRV reflects the innervation of the heart by the sympathetic/parasympathetic divisions of the ANS [4]. In the time domain, average and standard deviation of the normal-to-normal intervals (SDNN; the variability of the heart) and root mean square of the successive differences (RMSSD, vagally mediated HRV) will be calculated. In the frequency domain, low frequency (LF), high frequency (HF, cardiac vagal control) and total power will be assessed. Details of a HRV protocol we have employed are available [40].
(ii)Functional transcranial doppler sonography (fTCD) to assess cerebral artery blood flow at 10 weeks (short-term effect), to determine cerebrovascular benefits associated with the HRV-F, using Multi-Dop T digital with QL routine software (Compumedics Limited, www.compumedics.com.au). fTCD assesses real-time cerebral blood flow velocities/circulation in basal cerebral arteries of the participants in response to the intervention [41]. fTCD is a reliable method for measuring cerebrovascular changes, provides high temporal resolution and is least susceptible to artefact than other imaging techniques [41].

Electrocardiography (ECG) assessment and Functional transcranial doppler sonography will be performed using the same instruments (as per primary outcomes) at 6 and 12 months (long-term effects).

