### Excluded medications and treatments

To maintain data validity and ensure participant safety, all participants will remain on their prescribed medications as well as any commonly used assistive technologies that will not interfere with measures such as HRV or EEG. Use of medications will be monitored via a self-report assessment at each time point. Some medications may influence HRV, such as anti-hypertensives and anti-depressants. However, β-blockers have been shown to change HRV substantially [66], participants taking β-blockers will be excluded. In a recent study [26], it was concluded that the majority of medications taken by adults with SCI were not associated with any abnormal influences on HRV data. This included cardiac medications such as ace inhibitors, angiotensin II, anti- platelet, calcium channel blockers, muscle relaxants and anti-convulsants. Even though it is expected that these medications will have some influence on HRV measures, randomization should control any such affects. However, if the data suggests that medication usage is not balanced across the RCT arms, then medication usage will be adjusted for in the statistical analysis to limit potential confounding.

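### The exclusion list sets no cardiac-rhythm requirement, so people in persistent atrial fibrillation or flutter, or with a paced rhythm, can enter a trial whose primary outcome is heart rate variability

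*Protocol article*

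**What the plan says.** **Eligibility.** The Participants section opens its exclusions with "Exclusion criteria consist of: (i) evidence of severe cognitive impairment as determined by a neurocognitive screen". It then adds severe respiratory disorder or impaired respiratory function, severe psychiatric disorder, and prescribed β-blockers. The wording presents the list as complete. On age it admits people "aged 18–70 years with SCI living in New South Wales (NSW), Australia".

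**Primary outcome.** Under Primary physiological outcome measures, "HRV will be calculated at 10 weeks (short-term effect), in order to determine whether HRV-F results in improved autonomic nervous system function". The time-domain measures include the "average and standard deviation of the normal-to-normal intervals (SDNN; the variability of the heart"), alongside RMSSD, with LF, HF and total power in the frequency domain. The same section gives the interpretation: "HRV reflects the innervation of the heart by the sympathetic/parasympathetic divisions of the ANS". Transcranial doppler is the other primary outcome.

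**Exclusion to protect HRV.** Excluded medications and treatments bars β-blockers because they "have been shown to change HRV substantially". Participants on other cardiac medications may enter.

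**What is collected before randomisation.** Table 1 lists an eligibility checklist and the "ISCoS cardiovascular function dataset" at screening, and ECG/HRV at day 0. Randomization and blinding places the baseline assessment before allocation.

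**The concern.** A normal-to-normal interval is the time between two beats of sinus origin. In persistent atrial fibrillation or flutter there is no such series, and the beat-to-beat differences do not reflect vagal control. In a paced rhythm the device sets the intervals. The software still returns SDNN, RMSSD and spectral power, but the numbers no longer carry the meaning that the protocol gives them.

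The protocol already accepts validity of HRV as a reason to exclude, but applies it only to one drug class. It recruits to age 70, and its Background describes raised cardiovascular morbidity after spinal cord injury, so such rhythms cannot be assumed absent. At stake is the quality of a primary outcome in a trial planned on 50 analysed participants per arm, where one or two uninterpretable values carry some weight.

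**Working it through.** **1. Is the gap closed elsewhere?**

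- *Participants*: four exclusions, none on rhythm.
- *Table 1, screening*: a cardiovascular dataset is collected, but no stated criterion uses it, and its contents are not given.
- *Primary physiological outcome measures*: "HRV signal processing will be performed using Kubios HRV Premium software", with no rhythm requirement stated.
- *Secondary physiological outcome measures*: artefact removal is mentioned in the EEG text.
- *Control of bias*: all randomised participants are analysed as assigned.

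Nothing shown prevents an affected person from being randomised.

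**2. The plan's own power figure (context only).** Power analyses states 0.99 for effect size 0.3, 50 per group, four assessments and α = 0.05. Inputs: N = 100, m = 4, correlation ρ assumed. The noncentrality is N f² m / (1 + (m − 1)ρ) for the between-group test and N f² m / (1 − ρ) for group by time.

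- 0.3 read as Cohen's f: between-group power is 0.991, 0.964 and 0.921 at ρ = 0.3, 0.5 and 0.7. Group-by-time power is at least 0.9997.
- 0.3 read as Cohen's d (f = 0.15 for two groups): group-by-time power is 0.862, 0.957 and 0.998 at the same ρ.

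A power of 0.99 can be reached on either reading, so it does not settle which metric is meant. Both are carried below.

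**3. How likely is at least one affected participant?** The documents give no prevalence. Assume a proportion p of 0.5% to 3%, with participants independent. P(at least one) = 1 − (1 − p)^n.

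| p | n = 100 analysed | Expected number in 100 |
|---|---|---|
| 0.5% | 1 − 0.995^100 = 39% | 0.5 |
| 1% | 1 − 0.99^100 = 63% | 1 |
| 2% | 1 − 0.98^100 = 87% | 2 |
| 3% | 1 − 0.97^100 = 95% | 3 |

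**4. Chance imbalance.** With 50 per arm, ignoring stratification, a single case falls wholly in one arm. Two cases fall in the same arm with probability 49/99 = 49%. Three do so with probability (49 × 48)/(99 × 98) = 24%.

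**5. Dilution alone.** Suppose a share q cannot respond and the SD is unchanged. For a single 10-week comparison, two-sided 0.05 and 50 per arm, power = Φ(d(1 − q)√(50/2) − 1.96).

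| q | d = 0.6 (f = 0.3) | d = 0.3 |
|---|---|---|
| 0 | Φ(3.00 − 1.96) = 0.851 | Φ(1.50 − 1.96) = 0.323 |
| 2% | Φ(2.94 − 1.96) = 0.836 | Φ(1.47 − 1.96) = 0.312 |
| 3% | Φ(2.91 − 1.96) = 0.829 | Φ(1.455 − 1.96) = 0.307 |

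Dilution by itself is therefore small. The loss from added variance would come on top, but it needs an SD in sinus rhythm and a spread for the affected values. The documents give neither, so no figure is put on it.

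**The case against.** **Randomisation deals with it.** In expectation, yes. A reader might infer that the treatment effect would be biased, but allocation is 1:1 at random and nothing ties these rhythms to one arm. A person with the same abnormal rhythm at both visits also has a baseline value, and Statistical methods adjusts for relevant baseline scores. This stands: the harm is noise, dilution and chance imbalance.

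**It is processing detail.** A reader might extend the point to ectopic beats. The normal-to-normal definition implies that isolated non-sinus beats are not counted. The limit on correction belongs to HRV processing, for which the article points to a separate HRV protocol. That extension is not supported. The reply does not cover fibrillation, flutter or pacing, and eligibility is stated here as a complete list.

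**Intention-to-treat.** A reader might infer that the trial must either analyse invalid values or breach intention-to-treat. That does not follow. Treating an unusable recording as missing leaves the participant in the analysis, and the mixed model is the stated way of handling missing data.

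**Screening may already catch it.** The checklist is not shown and may ask about rhythm. Even so, the published list gives no ground on which to exclude.

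**Excluding people for one outcome is heavy.** Transcranial doppler is also primary, and this is an effectiveness trial. That is a fair trade-off. Against it, HRV-F itself uses HRV feedback to find each person's resonant breathing rate, so the same signal is needed to deliver the intervention.

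**Conclusion.** The point holds in a limited form. No stated figure is wrong and no two sections conflict. The complete exclusion list leaves out a condition on which the meaning of a primary outcome depends, although the protocol already excludes β-blocker users to protect that outcome.

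On the assumed prevalence of 0.5% to 3%, at least one affected participant among 100 has a probability of 39% to 95%. The expected number is only 0.5 to 3, so the effect on power from dilution is modest and the rest is unquantified variance and chance imbalance. The range is an assumption throughout.

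A reader might go further and estimate how far one participant who changes from sinus rhythm to fibrillation between visits would move an arm mean. The documents give no SD or size of change for that, and an entry criterion would not catch a person whose baseline ECG was normal. The conclusion concerns rhythms present at entry.

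**What to change.** Add a fifth exclusion to the Participants section: atrial fibrillation or flutter, or a paced rhythm. Apply it from screening information and confirm it on the baseline ECG, before randomisation. Because nobody is removed after allocation, the intention-to-treat set is untouched.

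No new procedure is needed, since the baseline ECG is already recorded before allocation. The baseline trace has to be looked at before the participant is released for randomisation. The check should not rest on the screening cardiovascular dataset alone, because the article does not show whether it records rhythm or pacing.

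The cost is that a few people become ineligible and generalisability narrows slightly. That includes the transcranial doppler primary outcome, to which those people could otherwise have contributed.
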